### Sample size calculation

The primary outcomes of the app effectiveness study are the changes in the prevalence of modern contraceptive use, STI testing, STI treatment, and SRH awareness. We propose to estimate the study’s sample size based on the prevalence of modern contraceptive use among the youth aged 18 to 30 years. According to the 2016 Uganda Demographic and Health Survey, the prevalence of modern contraception among the youth aged 18 to 30 years in Uganda is 30.2%. The study utilizes the sample size formula for Z test for two sample proportions used for behavioral studies to compute sample size estimates.

Sample size formula;$$ n=d\left(\frac{{\left({Z}_{1-\alpha /2}\sqrt{2p\left(1-p\right)}+{Z}_{1-\beta}\sqrt{\left({p}_1\left(1-{p}_1\right)+{p}_2\left(1-{p}_2\right)\right)}\right)}^2}{{\left({p}_2-{p}_1\right)}^2}\right) $$

Where:

*n* = sample size.

*d* = design effect.

*p*_1_ = the prevalence of modern contraception.

*p*_2_ = projected prevalence at the end of the study, so that (*p*_2_ − *p*_1_) is the magnitude of change you want to be able to detect.

*p =* (*p*_1_ +*p*_2_)/2.

*Z*_1 − *α*_= the z-score corresponding to desired level of significance.

*Z*_1 − *β*_ = the z-score corresponding to the desired level of power.

The table below shows the required sample size for each group with varying magnitude of change in proportions to be detected, different power sizes, and two-sided level of significance of 0.05.

The study will require a sample size of 435 participants per randomized group in order to obtain 90% power to detect a 15% change in the prevalence of modern contraception at a two-sided of 5% level of significance. The sample size estimations assumed no design effect i.e. d = 1. After adjusting for the 10% non-response rate, a sample size of 479 was computed leading to a total sample size of 958.

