**Methods:**

The study employs rigorous evaluation methods to ascertain the impact of the mobile application. We propose a randomized control trial study to determine the causal effect of the mobile phone app in creating awareness and increasing uptake of sexual and reproductive health services in Uganda. The main outcome of the impact evaluation is the percentage change in the SRH services and tools uptake, SRH knowledge and sexual behavior. We will also conduct a model-based incremental cost-effectiveness analysis (CEA) and budget impact analysis (BIA). The main outcomes of the economic evaluation will be the average cost per app user, cost per app service and tool provided. We will also test the in-app advertising model as a way to generate revenue to sustain the program subsidies and related costs.

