### Study outcomes

The primary outcome of the study is the magnitude of change in the SRH services uptake measured by the proportion change of modern contraceptives use and testing and treatment for sexually transmitted infections at month six. The secondary outcomes are changes in participant’s knowledge of SRH and sexual behaviors at month six.

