### Primary analysis

We will assess the differences at baseline between the intervention and control arms. Observed group differences for each variable will be summarized using means and proportions. The primary analysis will be an intention to treat analysis (ITA). The magnitude of change in proportion between the two groups provides a potentially unbiased estimate of the average treatment effect (ATE) of the SRH App. We will use a two-sample proportion Z-test to test the null hypothesis that the two sample changes in proportions are significantly different at month six at 5% level of significance. We will also carry out a difference in difference (DID) analysis to identify the magnitude of change as a result of the SRH App. We will also compare the changes in the different contraceptive methods and STI tests self-reported at six months by study arm.

We will conduct binary regression analysis with the primary outcome as the response variable and the participant characteristics as the explanatory variables. We shall adjust for any confounding influence that may arise from the participant belonging in any study arm or time point of data collection by adding the study arm and time point as explanatory variables in the regression model.

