### Secondary analysis

We are also interested in the effect of the SRH App among those who download and use the App. Using the data from the app developer, we shall construct a binary index of app use. We shall then conduct an instrumental variables analysis to obtain an estimate of the effect of app use on SRH uptake and awareness. We shall conduct the standardized test to verify whether the instrument has good predictive power in the first stage of the regression and whether it is valid in a multiple regression analysis with the observed characteristics included in the model.

We also further assess if SRH awareness is associated with changes in SRH uptake among the study participants in both arms of the study. We will construct an index for SRH awareness and the conduct a binary regression analysis with SRH uptake as the response variable and SRH awareness as the explanatory variable. We check the validity of the association in a multiple regression analysis with observed characteristics included in the model. Both adjusted and crude odds ratios with their corresponding confidence intervals and *p*-values will be reported. All results will be considered statistically significant at a 5% level of significance.

To assess acceptability and user-satisfaction, we will analyze the download and usability statistics and reviewer comments on the app from those randomized to receive the app. Further, we have included questions on acceptability and user satisfaction (user rating of the app) and will report simple proportions for each question.

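### The primary outcome is stated differently in different sections, with awareness primary in one and knowledge secondary in another, and 5% is the only significance level whether there are one, three or four primaries

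*Protocol article*

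**What the plan says.** Three sections of the protocol article name the outcome on which the trial is to be judged.

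- **Sample size calculation** gives four outcomes, in the plural: "The primary outcomes of the app effectiveness study are the changes in the prevalence of modern contraceptive use, STI testing, STI treatment, and SRH awareness". It then sizes the trial on modern contraceptive use alone.
- **Study outcomes** uses the singular: "The primary outcome of the study is the magnitude of change in the SRH services uptake". Uptake is measured by the "proportion change of modern contraceptives use and testing and treatment for sexually transmitted infections at month six". Awareness is not in this list. The secondary outcomes are changes in participants' "knowledge of SRH and sexual behaviors at month six".
- **Abstract, Methods** words it a third way: "The main outcome of the impact evaluation is the percentage change in the SRH services and tools uptake, SRH knowledge and sexual behavior".

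On significance, Sample size calculation uses a "two-sided level of significance of 0.05". Primary analysis tests whether "the two sample changes in proportions are significantly different at month six at 5% level of significance". Secondary analysis ends with: "All results will be considered statistically significant at a 5% level of significance". The article gives no composite definition, ordering of tests, split of the 5%, or requirement that all primaries succeed.

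**The concern.** The first two statements cannot both be followed. Suppose that at month six awareness differs between the arms but contraceptive use and the STI outcomes do not. Under the sample size section a primary outcome has been met. Under Study outcomes only a secondary one has. The same data would support opposite headlines, and an analysis plan that is faithful to one section breaks the other.

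The second issue follows from the first. Until the number of primaries is fixed, nobody can say whether a single 5% level protects the main claim. With one primary outcome it does. With three or four, it depends on what counts as success, which the article does not say.

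**Working it through.** **1. Count the primaries under each section.**

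| Section | Primary or main outcomes | Awareness / knowledge |
|---|---|---|
| Sample size calculation | 4: contraception, STI testing, STI treatment, awareness | awareness is primary |
| Study outcomes | 1 named (uptake), with 3 components | knowledge is secondary |
| Abstract, Methods | uptake, knowledge, sexual behaviour | knowledge is part of the main outcome |

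The count is therefore 1 if uptake is a composite, 3 if its components are tested separately, or 4 if the sample size section governs.

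**2. Are awareness and knowledge the same thing?** The section on baseline and follow-up assessments says that follow-up is meant to show the effect on awareness and uptake, and the matching data it lists are on knowledge and uptake. The terms appear to cover one domain. If they do not, awareness is primary in one section and absent from the outcomes listed in the other, which is still a conflict.

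**3. Family-wise error, if the primaries are separate and any one success counts.** With k independent tests at two-sided 5%, the error is 1 − 0.95^k.

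- k = 3: 1 − 0.8574 = 14.3%
- k = 4: 1 − 0.8145 = 18.5%

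Whatever the dependence, the error cannot exceed k × 5%, that is 15% or 20%. The article gives no correlations, so a range was assumed. One million draws of equally correlated normal statistics, rejecting beyond ±1.96, give:

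| Assumed correlation | k = 3 | k = 4 |
|---|---|---|
| 0.3 | 13.5% | 17.4% |
| 0.5 | 12.5% | 15.6% |
| 0.7 | 10.8% | 13.0% |
| 0.9 | 8.3% | 9.4% |

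These figures count rejections in either direction. Counting only those that favour the app, under independence, gives 1 − 0.975³ = 7.3% and 1 − 0.975⁴ = 9.6%, against a nominal 2.5%.

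**4. Would a multiplicity rule need a larger trial?** Inputs from Sample size calculation: p1 = 0.302, a 15% change read as absolute (p2 = 0.452), 90% power, two-sided 5%, design effect 1, 435 per group.

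First, the plan's own figure. The mean proportion is 0.377, and the printed formula gives

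(1.960 × √(2 × 0.377 × 0.623) + 1.2816 × √(0.2108 + 0.2477))² / 0.15² = (1.3433 + 0.8678)² / 0.0225 = 217.3, so 218 per group.

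The stated 435 per group is not reproduced. It equals 2 × 217.28 = 434.6 rounded up, which is the total for both arms. That is a separate matter, but it bears on the fix.

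Taking 435 per arm as stated, power for contraception is Φ[(0.15 × √435 − z × 0.6854) / 0.6771], where 0.6854 and 0.6771 are the two square roots above:

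- 5%, z = 1.960: 99.6%
- 5%/3 = 1.67%, z = 2.394: 98.6%
- 5%/4 = 1.25%, z = 2.498: 98.2%

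For 90% power at the split levels, contraception needs 280 (three primaries) or 296 (four) per arm. Both are below 435.

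**The case against.** The best defence is that there is only one primary outcome. Study outcomes uses the singular, Primary analysis fits a binary regression to the primary outcome as one response, and Secondary analysis treats uptake as one response variable. On that reading k = 1, no error is inflated, and the construction of the composite can sit in an analysis plan that is not shown. Multiplicity detail is also often left to that plan, and this is a condensed article about a pilot.

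Much of this stands. A reader might infer that three or four primaries are each formally tested at 5% and that any one success makes the trial positive. The article does not say so. Primary analysis states a single test at 5%, the sentence applying 5% to all results stands under Secondary analysis, and no success rule is given. The abstract says main rather than primary, so it is weaker evidence than the other two sections.

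Two further arguments are tempting but are not settled by the document. One is that STI treatment is unsuitable as a primary because its direction is ambiguous; if the construct is service uptake, more treatment is more uptake. The other is that knowledge is the outcome an information app will move most easily; this app also delivers products and subsidises them.

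The composite reading does not remove the conflict. It contradicts the four outcomes in the sample size section, and no rule is given for turning three components into one. An unseen analysis plan can add detail, but it cannot agree with both sections.

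**Conclusion.** The contradiction is real and is in the current text: awareness is primary in Sample size calculation, while Study outcomes gives uptake as the primary outcome and makes knowledge secondary. Which section is followed can decide whether the trial is called positive, so it should be resolved before analysis.

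The multiplicity part is conditional. If the primaries are separate, all are tested at 5% and any one success counts, the family-wise error is 14.3% (three) or 18.5% (four) under independence, and about 8% to 17% across the assumed correlations of 0.9 to 0.3. If a single composite is meant, there is no inflation, but the composite is undefined. The document does not support the flat statement that the trial runs three or four unadjusted primaries.

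**What to change.** State one primary set in the same words in the Abstract, Sample size calculation and Study outcomes, and place awareness/knowledge among the secondary outcomes, as Study outcomes already does.

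- **Simplest option:** month-6 modern contraceptive use as the single primary, since the sample size rests on it, with the STI outcomes secondary. The 5% level then needs no adjustment and N is unchanged.
- **If the uptake components stay as separate primaries:** test them by Holm, or in a fixed sequence starting with contraceptive use, and say so in Primary analysis. N need not change: at 435 per arm contraception keeps 98.6% power even at one third of 5%, if the 15% change is absolute. Power for the STI outcomes cannot be worked out from the article, which gives no baseline rates or target differences for them.

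This power statement depends on 435 per arm. If that figure is later corrected to the 218 that the printed formula gives, a Bonferroni split across three primaries would need 280 per arm for contraception. If the 15% is relative (30.2% to 34.7%), 435 per arm gives only about 30% power even at an unsplit 5%.

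The cost is wording in three places, plus a sentence in Primary analysis if several primaries remain. Some outcomes lose headline status or face a stricter threshold, and under a fixed sequence an STI result could not be claimed if contraception failed.

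### The primary outcome is defined differently in three sections, only modern contraceptive use is sized, and nothing says which result decides the trial

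*Protocol article*

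**What the plan says.** The protocol article defines the main or primary outcome in three places.

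- **Abstract, Methods:** "The main outcome of the impact evaluation is the percentage change in the SRH services and tools uptake, SRH knowledge and sexual behavior". This is three domains under one label.
- **Sample size calculation** lists four outcomes, in the plural: "The primary outcomes of the app effectiveness study are the changes in the prevalence of modern contraceptive use, STI testing, STI treatment, and SRH awareness".
- **Study outcomes:** one primary outcome, the change in uptake, "measured by the proportion change of modern contraceptives use and testing and treatment for sexually transmitted infections at month six". The next sentence reads: "The secondary outcomes are changes in participant’s knowledge of SRH and sexual behaviors at month six".

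Three further statements bear on the point.

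- Sizing rests on one outcome: "We propose to estimate the study’s sample size based on the prevalence of modern contraceptive use among the youth aged 18 to 30 years".
- Primary analysis describes a two-sample proportion Z-test at month six at the 5% level, and then a "binary regression analysis with the primary outcome as the response variable". It does not say which variable that is.
- Secondary analysis ends by saying that all results will be judged at the 5% level.

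**The concern.** Which outcome is primary is a protocol decision, because it determines which result answers the trial's question. Here awareness or knowledge is primary in one section and secondary in another. Sexual behaviour is part of the main outcome in the Abstract, absent from the sample size list, and secondary in Study outcomes.

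The analysis text does not settle the matter. It uses the singular for something that two sections describe as several measures, and it sets 5% without saying whether one, all or some combination must succeed. A reader of the results could not tell from this article which p-value was meant to be decisive. The authors could, without breaching the text, present as the main result whichever listed outcome came out favourably, and the nominal 5% would then not describe the error rate of the main claim.

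**Working it through.** **Step 1. Set the definitions side by side.**

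| Outcome | Abstract, Methods | Sample size calculation | Study outcomes |
|---|---|---|---|
| Modern contraceptive use | main, within uptake | primary (the only one sized) | primary |
| STI testing | not named; uptake only | primary | primary |
| STI treatment | not named; uptake only | primary | primary |
| SRH awareness or knowledge | main | primary | secondary |
| Sexual behaviour | main | not listed | secondary |

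Only modern contraceptive use is clearly primary under every definition. Awareness or knowledge and sexual behaviour change status between sections. I treat awareness and knowledge as the same domain, as the article appears to. If they are different, Study outcomes gives awareness no status at all, and the conflict remains.

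**Step 2. Count the listed primary outcomes.** Study outcomes names three components and Sample size calculation names four. The Abstract names three domains.

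**Step 3. Chance of at least one false positive.** The article states no overall error figure, so there is none to reproduce. Inputs: 5% per test (Primary analysis; Secondary analysis) and k = 3 or 4 from Step 2. Assumptions that are mine: the app has no effect on any outcome, and success on any one outcome would count.

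For independent tests the chance is 1 − 0.95^k:

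- k = 3: 1 − 0.8574 = 0.143, or 14.3%
- k = 4: 1 − 0.8145 = 0.185, or 18.5%

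The documents give no correlations, so I show a range for a common correlation between the test statistics, from simulated two-sided z-tests:

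| Assumed correlation | k = 3 | k = 4 |
|---|---|---|
| 0 | 14.3% | 18.5% |
| 0.5 | about 12.5% | about 15.6% |
| 0.9 | about 8.4% | about 9.3% |

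Every case exceeds 5%. The independent figures are the upper end of this range.

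**Step 4. What a smaller alpha would do to power.** This matters only if several primary outcomes are kept. Inputs from Sample size calculation: 30.2% baseline, 435 per arm, a 15% change, and the article's two-proportion formula. The article does not say whether 15% means percentage points or a relative change.

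| Reading of 15% | Power at alpha 0.05 | Power at alpha 0.0125 (0.05/4) |
|---|---|---|
| Percentage points, 30.2% to 45.2% | 99.6% | 98.2% |
| Relative, 30.2% to 34.7% | 29.7% | 14.2% |

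Any reassurance about power at a reduced alpha therefore depends on the percentage-point reading. The definition of p2 − p1 as the magnitude of change favours that reading but does not settle it. Neither reading gives the stated 90% at 435 per arm. That is a separate matter and does not affect this point.

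**The case against.** The strongest reply is that this is a condensed journal article. Multiplicity procedures, testing order and composite definitions are commonly left to a full protocol or SAP, and sizing on one of several primary outcomes is ordinary practice. The study is also called a pilot. Much of this stands: the absence of an alpha rule would not be a finding by itself. What it does not answer is that the article does state the primary outcome, three times, and the statements conflict. Pilot status does not remove the problem either, because the trial is sized for a formal two-sided test and presented as establishing a causal effect.

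Three stronger readings are tempting, and the documents do not support them.

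- **A useless app has a 14–23% chance of success.** Stated flatly, this requires independent tests and an any-one-wins rule, neither of which the article states. Independence is also doubtful: uptake is self-reported by the same participants, and treatment tends to follow testing. The upper end of 23% needs five outcomes, which no section lists. It comes from splitting uptake in the Abstract into the components given in Study outcomes.
- **The regression needs a composite, which would lose power.** The binary regression could be fitted once for each component, so no composite is implied. If Study outcomes does mean one composite, there is a single test and the 5% holds. A loss of power follows only if the app leaves STI testing and treatment almost unchanged, yet the app is meant to link users to testing. Take 435 per arm, contraceptive use rising from 30.2% to 45.2%, STI treatment of 5% and independence (the last two are assumptions). A 5-point rise in testing from an assumed 10%, 30% or 50% then gives power of 99.6%, 96.7% or 89.1% for an any-of-three outcome.
- **A composite should be ruled out.** Nothing in the article justifies that. A composite would be acceptable if it were defined in advance and sized.

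**Conclusion.** The point holds as an inconsistency in the definition of the primary outcome. The Abstract, Sample size calculation and Study outcomes sections cannot all be followed, Primary analysis refers to a single primary outcome without identifying it, and no statement says which result decides. This rests on the text alone.

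The effect on the error rate is conditional. If any one listed outcome could carry the claim, the false-positive chance is at most about 14% (three outcomes) or 19% (four) with independent tests, falling to about 8–9% at an assumed correlation of 0.9. If one outcome, or one defined composite, is fixed in advance, it is 5%. The correction should be made before enrolment, because it determines which result answers the trial's question.

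**What to change.** Make the Abstract, Sample size calculation, Study outcomes and Primary analysis sections give the same definition.

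The simplest way is to name modern contraceptive use at month six, compared between randomised arms at two-sided 5%, as the single primary outcome, because it is the only one sized. STI testing, STI treatment, awareness or knowledge, and sexual behaviour then become secondary, and the binary regression in Primary analysis names contraceptive use as its response. This leaves the alpha for the sized comparison unchanged, so it costs no power under either reading of the 15% change.

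If the sponsor prefers to keep several primary outcomes, state them identically throughout and control the overall 5% across them, for example with Holm. State also whether the 15% is in percentage points, because the power at a smaller alpha depends on it.

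The cost of the single-primary fix is wording. The article reports that the app prototype is still under development, so there is time. No more participants are needed. The downside is that a lone positive result on a non-primary outcome, such as STI testing or awareness, can no longer be presented as the main result.

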## Discussion

In this pilot study, we will develop a sexual and reproductive health services delivery and awareness phone application and assess its effectiveness in increasing awareness and uptake of sexual and reproductive health services among the youth aged 18 to 30 years using a randomized controlled design. The study will also assess the acceptability, usability, cost-effectiveness of this services delivery model. Further to this, the study will also assess effectiveness of in-app advertising as a way of generating revenues possible transition to scale. Existing evidence reveals that sexual and reproductive health programs tailored to the youth should be accessible, equitable, appropriate and effective [17]. The challenges affecting the youth and adolescents in low-income nations like Uganda include privacy, confidentiality, and limited SRH knowledge [11]. We hypothesize that the proposed App that will allow the youth to order for SRH tools and have them delivered to their preferred pick-up points presents an a private, confidential, youth-friendly and effective method of creating demand for sexual and reproductive health tools among the youth. The App will also enable the users to book for the services online from a pool of the partner clinics, and also have access to sexual and reproductive health information tips. The intervention provides subsidies inform of price cuts on the products and services to further incentivize the low-income youth to embrace safe sexual practices, increase use of family planning services, and other sexual and reproductive health services. Thus, our innovation reduces both the knowledge and financial barriers to access of SRH information and services by providing comprehensive SRH information and subsidizing SRH services. In the long run, the SRH App will be self-sustaining through revenues from in-app advertisements. The study helps in understanding 1) the causal effect of mobile phone applications and SRH service demand creation and uptake among youth age 18–30, 2) the cost-effectiveness of such interventions in low-income settings, and 3) the use of in-app advertisements for revenue generation to SRH services. If the study is successful, it will present policymakers and other stakeholders in Uganda, and internationally, with a viable services delivery model for increasing uptake of SRH services, tools, and awareness among the youth. The strength of this study lies in it’s innovativness to leverage mobile phones to provide the non-existent servics delivery model in the line of sexual and reproductive health services. The further applies a rigorous study design-a randomized controlled study design to evaluate the effcetiveness of the App. Even though the study is controlled, we are not able to control students in the control group interacting with with students in the trial arm of the study. This has potential for bias and a possibility of App services mis-use for tools that will be ordered online.

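### The sample size labels its 15% effect as a change to an end-of-study prevalence with no arm named, and 435 per group is not what the printed formula gives for 90% power

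*Protocol article*

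**What the plan says.** All inputs are in the protocol article under Sample size calculation. It cites a national survey: "the prevalence of modern contraception among the youth aged 18 to 30 years in Uganda is 30.2" percent. In the formula, p1 is that prevalence and p2 is the "projected prevalence at the end of the study, so that" the difference p2 − p1 "is the magnitude of change you want to be able to detect". No arm is attached to either value, and no change among controls is given. The method is named as a two-sample Z test for proportions, with a "two-sided level of significance of 0.05" and a design effect of 1.

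The result reads: "The study will require a sample size of 435 participants per randomized group", which is said to give "90% power to detect a 15% change in the prevalence of modern contraception". Allowing 10% for non-response, this becomes 479 per group and 958 in total.

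Under Primary analysis, the test asks whether "the two sample changes in proportions are significantly different at month six", comparing the two arms, and a difference-in-difference analysis is added. Under Control group/comparator, controls receive no intervention. The Discussion concedes that "we are not able to control students in the control group interacting with" app users. Under Study participants, enrolment is limited to students who report sexual activity in the past six months.

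**The concern.** There are two faults in the same few sentences.

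The first is a label. The effect is described as movement from today's prevalence to the prevalence at the end, but the trial tests app against control. The two quantities agree only if control prevalence stays at 30.2% for six months, and the article never states that assumption. It also gives some reason to question it: controls mix with app users, are told about the app at consent, and answer questions on contraception and STIs at follow-up. The 30.2% refers to all young people aged 18 to 30, not to sexually active students, so it is not an obvious control-arm value either.

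The second is arithmetic. The power sentence pairs 435 per group with 90% power for a 15% change, and the printed formula does not produce that pairing.

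This sentence is the only statement of what the trial can detect. A reader will use it to interpret the result, and anyone who re-computes the number per group will start from these definitions.

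**Working it through.** **Inputs** (all from Sample size calculation): p1 = 0.302; change = 15%, taken first as percentage points, so p2 = 0.452 and mean p = 0.377; two-sided α = 0.05 (z = 1.960); 90% power (z = 1.282); d = 1; stated n = 435 per group.

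**1. The plan's own figure.** The printed formula is

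n = [1.960·√(2p(1−p)) + 1.282·√(p1(1−p1) + p2(1−p2))]² / (p2 − p1)²

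- √(2 × 0.377 × 0.623) = √0.4697 = 0.6854; times 1.960 = 1.3433
- √(0.302 × 0.698 + 0.452 × 0.548) = √0.4585 = 0.6771; times 1.2816 = 0.8678
- n = (1.3433 + 0.8678)² / 0.15² = 4.8889 / 0.0225 = 217.3, so 218 per group

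The stated 435 is not reproduced. Twice the unrounded result is 434.6, which rounds up to 435, so the per-group figure equals the formula's total for both groups. The variants tried do not give it either: continuity correction 231, one-sided 177, 95% power 269, 99% power 379, a 10-point rise 478. The later figures do follow from 435: 435 × 1.10 = 478.5, hence 479 and 958.

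**2. Power at 435 per group.** Rearranging the same formula,

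power = Φ{ [(p2 − p1)·√n − 1.960·√(2p(1−p))] / √(p1(1−p1) + p2(1−p2)) }

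For 30.2% versus 45.2%: (0.15 × √435 − 1.3433) / 0.6771 = (3.1285 − 1.3433) / 0.6771 = 2.636, so power is 99.6%. With 431 analysed (479 less 10%) it is still 99.6%.

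**3. If 15% is relative.** Then p2 = 0.302 × 1.15 = 0.347. The formula needs 2,244 per group, and 435 per group has about 30% power. The text does not say which reading is meant; only the percentage-point reading is anywhere near the stated size.

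**4. If controls move.** The article gives no control-arm change, so the rises below are assumptions. The app arm is held at 45.2% and only controls rise from 30.2%.

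| Control rise (points) | Gap between arms (points) | Power, 435 per arm |
|---|---|---|
| 0 | 15 | 99.6% |
| 2 | 13 | 97.7% |
| 3 | 12 | 95.3% |
| 4 | 11 | 91.4% |
| 5 | 10 | 85.4% |
| 7 | 8 | 67.0% |

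Power falls to 90% at a rise of about 4.2 to 4.3 points (4.2 with 431 analysed).

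**5. If the gap between arms really is 15 points.** Power with 435 per arm is 99.6% with controls at 30.2%, 99.5% at 35.2% and 99.4% at 40.2%. The number needed for 90% power is 218, 227 and 231 per arm.

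**6. What 435 per arm delivers at 90% power.** Solving for the between-arm difference gives 10.5 points (control 30.2%), 10.8 (35%), 10.9 (40%) and 11.0 (45%).

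**The case against.** The best defence is that the calculation is already a between-arm one. It names a two-sample test, uses the two-group variance and gives its answer per randomized group. Since controls receive nothing, using the survey rate as the control value is the usual flat-control assumption, left unsaid. This largely stands: the fault is in the labels and the unstated assumption, not in the choice of formula.

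The figures in step 4 also depend on the app arm being fixed while controls alone rise. A shared trend, or an effect of repeated interviewing, would plausibly lift both arms and leave the contrast largely intact, and the comparison of changes removes shared movement. Only spill-over confined to controls behaves as in that table, and one-time passwords limit access to the app.

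A reader might infer that the 90% is overstated for the primary contrast and the trial underpowered, or that a null result could not count against a 15-point effect. The documents support neither. At 435 per arm, 90% understates the power for a 15-point gap, and it stays achievable until controls alone rise by about 4.2 points. With over 99% power for a true 15-point gap between arms, a null result would be strong evidence against one.

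Finally, the sample size table that the section mentions is not in the text available, so arm labels or assumptions in it could not be checked. The definitions and the power sentence in the text would still need correcting.

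**Conclusion.** The point holds as a labelling fault plus an arithmetic mismatch, not as a shortage of power. The effect is worded as a change to an end-of-study prevalence with no arm named, while the test is app versus control, so flat controls at 30.2% are assumed without being stated. On the percentage-point reading, the printed formula gives 218 per group for 90% power; 435 matches the total for both groups, and 435 per group gives about 99.6%. Why the figure doubled is not stated, so a total mislabelled as per group is an inference from the arithmetic.

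The error is in the conservative direction for the planned size. It would turn against the trial only if controls alone rose by more than about 4.2 points with the app arm at 45.2%, or if the number were cut to 218 on the same definitions. In that second case power would be 90% with flat controls, but about 80% after a 2-point control rise and 57% after a 5-point rise.

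**What to change.** In Sample size calculation:

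- Define p1 as the expected month-six prevalence in the control arm and p2 as that in the app arm, both among eligible students. If 30.2% is kept for p1, state that controls are assumed not to change.
- State that 15% means percentage points between arms.
- Replace the power sentence with what the planned size delivers: 435 analysed per arm gives 90% power for a between-arm difference of about 10.5 points (control 30.2%) to 11 points (control 45%), and about 99% power for 15 points.

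The cost is a few lines of rewording. Recruitment, randomization and the analysis do not change. A short table of power under assumed control-arm rises would help a reader but is optional.
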